### Recruitment

Consecutive, consenting seniors (aged ≥65 years) will be recruited from seniors independent living or supportive living residences in greater Edmonton.

#### Inclusion Criteria (All Criteria Must Be Met)

These include: (1) age ≥65 years with a documented diagnosis of diabetes and hypertension, and (2) adequate English fluency, both verbal and written.

#### Exclusion Criteria (Any 1 Sufficient to Exclude)

These include: (1) SBP level >220 mmHg or diastolic BP level >110 mmHg on screening BP measurement (WatchBP [Microlife Corp., Widnau, Switzerland]); (2) heart failure; (3) severe cognitive impairment, defined as a score of ≥5 on the Short Portable Mental Status Questionnaire [37]; (4) severe depression (Patient Health Questionnaire [PHQ-8] ≥15) [38]; (5) foreshortened life expectancy (<1 years); (6) participation in a concurrent cardiovascular trial; and (7) currently receiving case management services for cardiovascular risk factor control.

### Telemonitoring Intervention

The telemonitoring system will be built in collaboration with TeleMED (www.telemeddiagnostic.com). TeleMED, a Canadian company specializing in the electronic management of noninvasive diagnostic test data, will provide their services in-kind. All patients will receive a validated electronic upper arm oscillometric BP device (A&D Ltd. UA-651BLE; San Jose, CA) and a set top box that will enable wireless transmission of BP readings. This equipment will remain in their residence for the duration of the study. All patients will be shown how to view their BP readings on their device. Pushing a single button activates the device and initiates a BP measurement, which is autotransmitted to the set top box via a Bluetooth low-energy connection. Once set top box receives the data, it encodes the data to prevent “sniffing” by a third party. Without any further action required by the patient, the data are sent to a dedicated research server. The server decodes the data and encrypts it using the Advanced Encryption Standard with 256-bit key and inserts the encrypted data into the database. The research server is physically located at the University of Alberta in a secure facility accessible only to authorized personnel. The data are then securely pushed to TeleMED, where it is summarized in a web portal for provider use.

Patients will be instructed to perform all measurements according to recommended techniques for home BP measurement (Table 1). Four measurements will be taken daily for 1 week. If BP is uncontrolled (high or low), this 1-week of measurements will be done each month until BP is in the therapeutic range. Once controlled, the 1-week protocol will be repeated every 3 months, as recommended by contemporary guidelines [6]. Teletransmitted BP readings will be summarized within the health portal and an overall weekly mean will be calculated (first-day measurements will be discarded and the subsequent 24 measurements taken over the next 6 days will be averaged) [6]. This mean will be used for clinical management decisions. Temporal trends will be plotted to graphically summarize the data for provider use.

**Table 1 table1:** Blood pressure measurement.

Method	Details
24-hour ambulatory BP^a^monitoring	BP readings will be taken every 15 minutes during the daytime and every 30 minutes at night with a Spacelabs 90227 device. Twenty-one readings during the daytime and 7 during nighttime will be required for a successful study [ 39]. Otherwise, a repeat study will be necessary. Patients will be given a diary to record the times that they retire to and arise from bed. Day and night intervals will be defined according to these patient-reported times and used to determine the daytime and nighttime BP averages. Timing of drug administration will also be recorded. Patients will also be instructed to go about their daily activity but refrain from exercising for the duration of the monitoring period and to stand still with their arm at their side when the monitor cuff is inflating.
Home BP measurement	Two measurements 1 minute apart will be taken in the morning between 0800 and 1000 and 2 measurements will be taken in the evening between 1800 and 2200 taken using the A&D home device. This will be done on 7 consecutive days for 1 week. If BP is uncontrolled (high or low), this 1-week measurement protocol will be repeated each month until BP is within the therapeutic range. Once controlled, the 1-week protocol will be repeated every 3 months.
Automated office BP	Three reading average in both arms taken while seated plus 1 supine reading and 1 standing reading taken at 1 min and 3 min using the WatchBP device.

^a^BP: blood pressure

BP teletransmission will occur in all study arms but will be used differently in each:

Enhanced usual care: Home BP readings will be teletransmitted for data collection purposes but neither patients nor providers will have access to the teletransmitted readings. High BP levels that trigger safety alerts to research personnel are the only exception, patients and their primary care providers will be made aware of these (see safety end points below). This is nevertheless considered “enhanced” usual care because patients receive a home BP monitor, are taught how to measure home BP, and are encouraged to take BP readings to appointments with their providers. In addition, they will be reminded to perform a home BP series each quarter for study outcome purposes, which will encourage self-monitoring. This reflects contemporary Canadian recommendations [6]. A summary of the Canadian hypertension guidelines will also be faxed to each primary care provider at the time of patient enrolment [6]. Recognizing that it takes years for guideline adoption to occur, we suspect that many patients in this arm will be managed solely using office BP measurements despite the potential availability of patient-reported (but not teletransmitted) home BP readings.Telemonitoring alone: Home BP series mean, trends, and individual readings will be faxed to the primary care provider with a 1-page summary of Canadian guidelines for BP thresholds, targets, and treatments [6].Telemonitoring plus protocolized case management: Patients in this arm will each be assigned a pharmacist case manager who holds full prescribing privileges and who will (1) administer health behavior modification counselling, teach BP self-monitoring, and monitor medication adherence; (2) review telemonitored health portal BP summaries and make protocolized therapeutic adjustments if appropriate (Figure 2); (3) fax a summary of these adjustments to the participant’s primary care provider (to make them aware of treatment changes); and (4) facilitate communication between patients and providers.

Pharmacare (www.mypharmacare.ca), an Alberta company specializing in pharmaceutical service delivery, will provide pharmacist case managers as an in-kind contribution to the study. Pharmacare case managers hold full drug prescribing licences, enabling them to independently initiate and titrate drugs. To ensure full guideline concordant standardization of the intervention, case managers will undergo a training session with a group of clinical experts from the University of Alberta Hypertension Clinic (who also serve on the executive of Hypertension Canada) on home BP monitoring and hypertension guidelines before study initiation.

Medication regimen adjustments will be performed according to a guideline-concordant protocol [6]. Drugs will be added in the following order: angiotensin-converting enzyme inhibitor or angiotensin receptor blocker, dihydropyridine calcium channel blocker, thiazide diuretic, beta-blocker, spironolactone, doxazosin, clonidine, and hydralazine. Drugs will be reduced or stopped in reverse order. When initiating new agents, the longest-acting agents in each class will be used.

**Figure 2 figure2:**
[figure not shown]
Case manager protocol for antihypertensive drug titration.

### Data Collection Including End Points

Unless otherwise indicated, data will be collected at baseline, 6 and 12 months after randomization. Study personnel will collect data using standardized case report forms. Home BP series data will then be sent to secure servers housed within the Department of MedIT, Faculty of Medicine and Dentistry, University of Alberta and then forwarded to the Web portal.

Baseline data collection will include(1) demographics and health behaviours: age, sex, race, marital status, smoking, and alcohol intake; (2) past medical history: atrial fibrillation, dyslipidemia, coronary artery disease, stroke or transient ischemic attack, peripheral vascular disease, chronic kidney disease (glomerular filtration rate ≤60 mL/min and/or proteinuria), syncope, bradyarrhythmias, pacemaker, and history of hyponatremia, hyperkalemia, or hypokalemia; (3) past diabetes-related information: duration of disease, presence of retinopathy, neuropathy, nephropathy, amputation, symptomatic hypoglycemia, and use of insulin; (4) medication history including antihypertensive drugs: name, type, dosage, and frequency. This will be based on self-report and then will be cross-indexed with the patient’s pharmacy medication record; (5) anthropomorphic indices: height, weight, body mass index, and waist circumference; (6) upper mid arm circumference (to determine proper cuff size): measured using a tape measure half way between the acromion and the olecranon with the arm at heart level; (7) 24-hr ambulatory BP, home BP series, and pulse rate: BP will be measured according to recommended techniques (Table 2) using validated devices [40]. Three screening BP measurements will be taken while seated in each arm at baseline with the validated WatchBP office automated device to determine if exclusion criteria are present [41]. Lying and standing BP at 1 and 3 minutes will also be taken. A 24-hr ambulatory BP and mean 24-hour heart rate will be measured using the validated Spacelabs 90227 monitor (Snoqualmie, Wash) [42]. A home BP series taken with the UA-651BLE oscillometric home device (A&D Ltd., San Jose, CA) will be performed as outlined (Table 2). (8) Laboratory investigations will include serum sodium, potassium and creatinine; glycated hemoglobin (A1c); lipids (total cholesterol, high-density or HDL cholesterol, low-density or LDL cholesterol, triglycerides), urinary albumin or creatinine ratio and electrocardiogram; (9) Montreal Cognitive Assessment Scale **:**validated cognitive assessment instrument [43]; (10) Clinical Frailty Score: a validated 9-point instrument, with frailty defined as a score of 5 or more [44]; (11) health care use in past year includes physician visits, emergency department use, and hospitalizations ascertained through patient self-report and by linking to provincial administrative data sources and the provincial electronic health record; (12) quality of life and utility measurement: assessed using the EQ-5D [45]; (13) depression/anxiety measured using the Patient Health Questionnaire (PHQ-8) for depression [38] and the Generalized Anxiety Disorder Scale (GAD-2) for anxiety [46] These end points are being evaluated to ensure that increased monitoring does not lead to greater depression or anxiety via adoption of the “sick role” [35]; and (14) satisfaction with medical care: assessed similar to other studies that we have conducted [47-49] using the validated Patient Satisfaction Questionnaire (PSQ) [50], scored on a 5-point Likert Scale.

**Table 2 table2:** Costing data for economic analysis.

Identification	Measurement	Valuation	Comments	

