### Analytic Plan for Major Outcomes

#### Aim 1: Effectiveness of Telemonitoring ± Protocolized Case Management

All primary analyses will be conducted according to the intention-to-treat principle. The primary outcome is the 1-year change in proportion of patients with overall 24-hour SBP in the optimal range (SBP is used because it is a stronger predictor of risk and because diastolic BP is rarely elevated in seniors [10]). We will use 24-hour ABPM because it is the gold-standard measurement method and the best validated clinical trial BP end point [40]. The 24-hr ABPM therapeutic range will be 110-129 mmHg in patients aged 65-79 years and 110-139 mmHg in those ≥ 80 years. Justification for the upper thresholds chosen is based on current guidelines that specify an overall 24-hour ABPM of ≥130 mmHg as high in all patients, including those with diabetes [6]. In patients ≥80 years, we will allow the option of a higher 24-hour target of <140 mmHg (ambulatory BP threshold definitions of normal versus high are lower than office BP thresholds; therefore, this threshold is analogous to the Canadian guideline concordant <150 mmHg office BP target that is allowed in older frailer patients [6]).

Major secondary outcomes will include the change in mean 24-hour SBP and diastolic BP (overall, daytime, and nighttime). Home BP and the automated BP measurements taken at each study visit will be examined similarly. Additional major outcomes will include postural BP changes and changes in A1c, lipids, anthropomorphic indices, quality of life, depression/anxiety, satisfaction with medical care, resource utilization, and the safety end points described previously.

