##### Data Analysis

First, variables will be examined descriptively and graphically, including assessments of temporal trends and tests of normality. Second, the 6-month and 1-year mean change from baseline in each outcome will be calculated and compared between study arms (each intervention arm to the control arm, then between intervention arms) using chi-square tests for dichotomous outcomes and unpaired *t*-tests for continuous outcomes. Third, multivariable predictors of the 1-year change in a given outcome will be identified using appropriately constructed and calibrated logistic regression models for dichotomous outcomes (including the primary outcome) or linear regression models for continuous ones. Initial models will adjust for age, sex, SBP, and residential site (eg, Greater Edmonton Foundation versus Rosedale). Examples of additional covariates that may be examined include sociodemographic variables, comorbidities, baseline medications, primary care physician, and tests of potential interaction.

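### The depression and anxiety scales are collected to make sure monitoring does no harm, but the analyses described for them look only for a difference and cannot support that assurance at the planned size.

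*Protocol article*

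**What the plan says.** In the protocol article, under Data Collection Including End Points, baseline item (13) introduces the PHQ-8 for depression and the GAD-2 for anxiety. It gives the reason for collecting them: "These end points are being evaluated to ensure that increased monitoring does not lead to greater depression or anxiety". Both are measured again at 6 and 12 months.

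The Aim 1 section gives them their rank: "Additional major outcomes will include postural BP changes and changes in A1c, lipids, anthropomorphic indices, quality of life, depression/anxiety".

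The Data Analysis section then describes one scheme for every outcome. Mean change from baseline at 6 months and at 1 year is compared between each pair of arms "using chi-square tests for dichotomous outcomes and unpaired *t*-tests for continuous outcomes". A further step models the 1-year change by logistic regression for dichotomous outcomes "or linear regression models for continuous ones". The initial covariates are age, sex, SBP and residential site, and others may be examined. The baseline mood score is not named.

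For these two scales the article states no acceptable worsening and no rule based on a confidence interval.

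**The concern.** The stated purpose and the stated method answer different questions. The purpose is to be able to say that mood does not get worse. A t-test, a chi-square test or a regression coefficient judged against zero asks whether a difference can be detected. Failing to detect one shows absence of harm only if the interval around the estimate is narrow enough to exclude a worsening that matters. Nothing in the article ties the conclusion to that interval.

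At stake is a possible false reassurance. If monitoring caused a modest average worsening of mood, the described analyses could easily return a non-significant result, and the text offers no other route from the data to the assurance it says these scales are there to give.

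**Working it through.** **Inputs**
- Evaluable patients per arm: about 80 (Sample Size Considerations). The attrition step reproduces: 80 / (1 − 0.20) = 100 recruited per arm, 300 in total.
- Two-sided alpha: 0.05 (same section, stated for the primary outcome).
- SD of PHQ-8 or GAD-2 change: not given. Results are in SD units. For PHQ-8 points I assume an SD of 3 to 5. I make no such assumption for GAD-2.
- The article gives no power or precision figure for either scale, so there is none to reproduce.

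**Step 1: precision.** The standard error of a difference between two arms is SD × √(2/80) = 0.158 SD. The 95% half-width is 1.96 × 0.158 = 0.31 SD. In PHQ-8 points, using the t quantile on 158 degrees of freedom, this is 0.94 for SD 3, 1.25 for SD 4 and 1.56 for SD 5.

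**Step 2: what a non-significant result allows.** A result is non-significant when the observed difference lies between −0.31 and +0.31 SD. The upper confidence limit can then lie anywhere from 0 to 2 × 0.31 = 0.62 SD. With SD 3 to 5, the top of that range is 1.9 to 3.1 PHQ-8 points (0.62 × 3 and 0.62 × 5). The same p > 0.05 can therefore come with an interval that excludes any worsening or with one that leaves a sizeable worsening open.

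**Step 3: how often a modest worsening is missed.** Power is Φ(d / 0.158 − 1.96), where d is the true worsening in SD units.

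| True worsening | PHQ-8 points if SD is 3 to 5 | Power | Non-significant |
|---|---|---|---|
| 0.2 SD | 0.6 to 1.0 | 0.244 | 76% |
| 0.3 SD | 0.9 to 1.5 | 0.475 | 52% |
| 0.4 SD | 1.2 to 2.0 | 0.716 | 28% |
| 0.5 SD | 1.5 to 2.5 | 0.885 | 12% |

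The smallest worsening detectable with 80% power is (1.96 + 0.84) × 0.158 = 0.44 SD.

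**Step 4: is attrition the cause?** With all 100 per arm evaluable, the half-width is 0.28 SD, and worsenings of 0.2 and 0.3 SD are still non-significant in 71% and 44% of trials (1 − 0.293 and 1 − 0.564).

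**Step 5: could a margin be met?** If there is no true harm, the chance that the upper limit falls below a margin m is Φ(m / 0.158 − 1.96). At 80 per arm this is 0.244, 0.475, 0.716 and 0.885 for m = 0.2, 0.3, 0.4 and 0.5 SD. A tight margin would usually not be met; a margin near 0.5 SD usually would be.

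**Step 6: adjusting for the baseline score.** If baseline and follow-up scores have equal variance and correlation ρ, the adjusted analysis has (1 + ρ)/2 times the variance of the change-score analysis. It is therefore more precise whenever ρ is below 1. The gain cannot be quantified here because the article gives no ρ.

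**The case against.** The strongest defence is that these are additional outcomes in a condensed article. Neither scale is in the list of safety end points, the Objectives state no non-inferiority aim for mood, and the clause with 'ensure' is a one-line reason for collecting two questionnaires. A margin for such an outcome may properly sit in the full protocol or analysis plan, which are not shown. This stands: the absence of a margin is not the point. What remains is that the article states both a purpose and a method, and the two do not fit.

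Several stronger readings are tempting, and the document does not support them.

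- *That the t-test is the only analysis.* It is not. Chi-square tests are allowed for dichotomous outcomes, and regression follows. These still estimate or test a difference and set no bound on harm, and the regression covers only the 1-year change.
- *That depression is otherwise unwatched.* A PHQ-8 score of 15 or more excludes a patient at entry and triggers Data and Safety Monitoring Board follow-up later. This protects individuals; it does not compare arms, would not show a modest average shift, and does not cover the GAD-2.
- *That a non-significant result will be read as no harm.* A reader might infer this, but no section says so, and nothing prevents the trial from reporting intervals.
- *That modest harm would be missed in most trials.* This depends on the size of the worsening and the assumed SD. It holds at 0.2 SD, barely at 0.3 SD, and not at 0.4 SD or above.
- *That the control arm, which also self-measures, undermines the claim.* The abstract and the Objectives already frame safety relative to enhanced usual care, and 'increased' monitoring reads naturally as increased relative to that arm.

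A formal margin is also no cure-all, as step 5 shows, which is a reason to treat it as optional.

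**Conclusion.** The point holds as a mismatch between purpose and method. An aim to ensure "does not lead to greater depression or anxiety" cannot be met by analyses that look only for a difference when the planned size leaves a half-width of about 0.31 SD. A true worsening of 0.2 to 0.3 SD would go undetected in about 52% to 76% of trials.

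The SD-unit figures rest on 80 evaluable patients per arm, a two-sided 5% level and approximate normality of the mean difference. The translation into PHQ-8 points rests on the assumed SD of 3 to 5. The point concerns how additional outcomes are analysed and described. It does not bear on the primary outcome, and it does not show that the trial will misreport these scales.

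**What to change.** Either of two changes resolves it.

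1. In Data Analysis, add for the PHQ-8 and GAD-2 that the between-arm difference at 6 and 12 months will be estimated with adjustment for the baseline score and reported with its 95% confidence interval. Any statement that depression or anxiety was not greater should rest on the upper limit. If that claim is to be made formally, the sponsor should fix the acceptable worsening before data are seen. Where the upper limit does not support the claim, the report should say that harm was not excluded.
2. Alternatively, change 'ensure' to 'assess' in Data Collection Including End Points, so that the purpose matches the analyses described. Reporting the adjusted difference with its interval would still be the better analysis.

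The cost is a few sentences and no new data, since both scales are already collected at all three visits. The downside is that the trial may have to report that a modest worsening was not excluded.

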**Program Development**				
Health care professional time (physician, nurse, pharmacist)	Estimated hours for each health care professional to create care algorithm (algorithm start-up costs); Estimated hours for staff training to administer care algorithm (training costs)	Alberta Health Services wage rates, Alberta Health Care Insurance Plan/Alternate Funding Plan	Cost per patient estimated by plausible number of patients in program/managed per staff	
IT infrastructure	Equipment required to setup BP^a^telemonitoring and hours of IT support will be estimated from local experience and TeleMED input.	Wage rates. Price lists of IT equipment from manufacturer.	Costs apportioned over # of patients monitored in region over 5 years (estimated lifespan of equipment).	
**Program Delivery**				
Equipment	Number of home BP cuffs (standard and telemonitoring)	List price	Includes expected lifetime/repair costs and replacement.	
Internet/data	Mobile phone device/data plan used for telemonitoring (tested in sensitivity analysis).	Local cost of lowest priced suitable service	Included in sensitivity analysis, may be paid by health provider or patient (societal perspective)	
Medication use	Type, dose, frequency, and duration of use.	Alberta Blue Cross		
Health care professional time (pharmacist)	Estimated hours for staff to administer care algorithm (ongoing costs)	Alberta Health Services wage rates, Alberta Health Care Insurance Plan/lternate Funding Plan	Cost per patient estimated by plausible number of patients in program/managed per staff	
Staff costs/infrastructure	IT support/telemedicine portal/fax costs	TeleMED	Costs apportioned over # of patients monitored in region over 5 years.	
